# Precision Family Spirit: a pilot randomized implementation trial of a precision home visiting approach with families in Michigan—trial rationale and study protocol

**DOI:** 10.1186/s40814-020-00753-4

**Published:** 2021-01-06

**Keywords:** Precision science, Precision public health, Implementation science, Hybrid design, American Indian, Pregnancy and childbirth, Randomized controlled trials, Home-visiting

## Abstract

**Background:**

Home visiting is a well-supported strategy for addressing maternal and child health disparities. However, evidence-based models generally share implementation challenges at scale, including engagement and retention of families. Precision home visiting may address this issue. This paper describes the first known pilot randomized implementation trial of a precision home visiting approach vs. standard implementation. Primary aims are to: 1) explore the acceptability and feasibility of a precision approach to home visiting and 2) examine the difference between *Standard Family Spirit* and *Precision Family Spirit* on participants’ program satisfaction, client-home visitor relationship, goal alliance, and the impact of these factors on participant engagement and retention. Secondary aims are to explore potential differences on maternal behavioral and mental health outcomes and child development outcomes to inform sample size estimations for a fully powered study.

**Methods:**

This is a pilot Hybrid Type 3 implementation trial. Four Michigan communities primarily serving the Native American families and already using *Family Spirit* were randomized by site to receive Standard Family Spirit or Precision Family Spirit. Participants include *N* = 60 mothers at least 14 years of age (pregnant or with a newborn < 2 months of age) currently enrolled in Family Spirit. Precision Family Spirit participants receive core lessons plus additional lessons based on needs identified at baseline and that emerge during the trial. Control mothers receive the standard sequence of Family Spirit lessons. Data is collected at baseline (< 2 months postpartum), and 2, 6, and 12 months postpartum. All Precision Family Spirit participants are invited to complete qualitative interviews at study midpoint and endpoint. All home visitors are invited to participate in focus groups between study midpoint and endpoint. Exploratory data analysis will assess feasibility, acceptability, client-home visitor relationship, retention, adherence, and potential differences in intervention outcomes.

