### Participants

Our target population for recruitment is women who are *either* pregnant or have a baby no older than 2 months of age. All study participants must be at least 14 years of age and already enrolled in the Family Spirit program in their community. Since 2013, the CAIH and the ITC of MI have partnered on implementing the Family Spirit model across participating tribal communities. The ITC of MI has a strong infrastructure to support the incorporation of a research study into their existing home visiting programming.

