### Exclusion criteria

Inability to participate in full intervention or evaluation (e.g., planned move, scheduling conflicts, etc.)

Ambiguous cases based on unclear age at conception or unclear gestational age are reviewed by the Study Management Team before being deemed eligible for recruitment. Home visitors conduct informed consent procedures with all eligible participants. All participants must provide informed consent or assent to participate. Participants under age 18 must have parent/guardian consent. The first participant gave consent on June 25, 2019, and the first baseline assessment was completed on June 26, 2019.

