### Standard Family Spirit

Mothers at the control sites receive Family Spirit as usual, per existing ITC of MI program policies and procedures. In the standard of care, families receive regular home visits, delivered in the same sequence until 3 years postpartum (63 lessons total). Because the duration of enrollment for this pilot study is from pregnancy to 12 months postpartum, Standard Family Spirit participants should receive 47 lessons total. Home visitors at Standard Family Spirit sites use the Care4 platform to track their clients. They receive notifications about high depression scores, risk of self-harm, and potential domestic violence issues, but they do not receive notifications about other risk categories (first-time mom, substance use, nutrition, sexual and reproductive health) that would inform tailoring sequences in the Precision Family Spirit implementation approach. Details on the rationale for selecting these risk categories have been described elsewhere [9, 16].

In both arms of the study, home visitors provide referrals and connections to community agencies and services as needed. Existing procedures are in place to link participants to assistance that is available in their area. Home visitors often act as navigators and advocates for the families they serve. In addition, participant transportation to and from doctor and clinic appointments is common and will continue for enrolled participants in each arm.

The study team recognizes that differences may be small regarding number of prescribed lessons between Precision Family Spirit and Standard Family Spirit participants, but implementation outcomes may be potentially detectable because we are measuring program participant acceptability, satisfaction, quality of relationship between home visitor and client, retention, and adherence.

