### Data collection time points

Participant assessments include maternal self-reports using Care4 and an interview (Table 2). Self-reports are conducted in participants’ homes, another private location, or via text/email on an as needed basis. Data is recorded on either a tablet, computer, or paper. If data is collected on paper, the home visitor enters the data into Care4 upon her return to the office. In some cases, assessments are conducted via text or email, once the home visitor discusses on a case by case basis with the study management team. For example, if a home visit is cut short, assessments may be completed post-visit by the participant. A secure link is sent via text or email with instructions on how to complete and submit. All participants will be assessed at four timepoints: baseline, 2 months, 6 months, and 12 months postpartum. Each assessment timepoint is estimated to take participants between 30 min and 1 h to complete. In an effort to mitigate participant time burden, home visitors complete assessments with participants during already-scheduled visits, by scheduling a separate visit, or by emailing or sending links to participants via SMS to complete the forms on their own time. Precision Family Spirit participants may also be asked to participate in a phone interview at study midpoint (between 4.5 and 6.5 months postpartum) and study endpoint (between 11 and 13 months postpartum), adding an additional 15–20 min of participant time burden for each interview completed. The purpose of these interviews is to further contextualize data being collected as part of the quantitative assessment.

**Table 2 Tab2:** List of hybrid trial objectives and evaluation measures

Pilot trial objectives	Instrument	Timepoint			
		Baseline	2 months postpartum	6 months postpartum	12 months postpartum

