#### Primary outcomes

Our primary outcomes of interest include participant acceptability, satisfaction, quality of relationship between home visitor and client, retention, and adherence. Acceptability is measured from the perspective of the participant using a 15-item scale [16] administered at study midpoint and endpoint. Satisfaction is captured through a 34-item questionnaire used in the Family Spirit trials and adapted specifically for this study and administered at midpoint (around 6 months postpartum) and endpoint. All Precision Family Spirit participants are invited to participate in a short qualitative interview to further explore acceptability and satisfaction using an 11-item interview guide. In addition, we will explore home visitor acceptability and satisfaction through focus group discussions that follow a 9-item interview guide. The quality of the relationship between home visitor and client is captured using the short version of the Working Alliance Inventory (WAI) administered to both participant and home visitor. The WAI measures three domains of the relationship: goal alignment, task alignment, and bond. Retention is measured by comparing the number of participants who drop out in each study arm. Adherence is measured by comparing the percentage of retained participants in each study arm who completed their lessons as prescribed.

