#### Secondary outcomes

As part of the Hybrid Type 3 approach, we also monitor specific maternal behavioral and mental health outcomes and child physical and social-emotional development outcomes.

Maternal substance use is measured at all assessment timepoints (baseline, 2, 6, and 12 months postpartum) using an adapted version of the World Health Organization’s validated Alcohol, Smoking and Substance Involvement Screening Test (ASSIST) [23, 24]. The ASSIST screens for all levels of problem or risky substance use (alcohol, illegal drugs, prescription drugs, and tobacco use). A risk score is provided for each substance, and scores are grouped into low, moderate, or high risk.

Maternal depression is measured at all timepoints (baseline, 2, 6, and 12 months postpartum) using the validated Edinburgh Postnatal Depression Scale (EPDS) [25]. The EPDS is a 10-item self-rating scale that was specifically designed for women who are pregnant or have just had a baby. However, it has also been shown to be an effective measure for general depression in the larger population [26].

Parent feeding practices are measured at 2, 6, and 12 months postpartum using an assessment developed by the study team. It is adapted from a child feeding assessment used in two other CAIH randomized trials in Southwest Native American communities [27, 28]. The assessment will be used to assess feeding practices, introduction of complementary feeding and introduction of sugar sweetened beverages among newborns and infants.

Maternal parenting knowledge is measured at all timepoints (baseline, 2, 6, and 12 months postpartum) using a 10-item assessment developed by the study team and tied to core Family Spirit curriculum content.

Other maternal outcomes are measured at all timepoints (baseline, 2, 6, and 12 months postpartum) using short screening tools or measures: overall quality of life is measured using the EuroQol [29], maternal self-efficacy is measured using the Parental Locus of Control scale [30], parental stress is measured using the Perceived Stress Scale 4 [31], substance abuse/domestic violence risk is measured using the Institute for Health and Recovery Integrated Screening Tool [32], and client priority outcomes are measured using the Top Problems measure [33]. Each measure included in this assessment is valid and reliable, with some having been shortened through a previous secondary data analysis using Item Response Theory Methods [34].

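### Baseline can fall anywhere from pregnancy to 2 months postpartum while follow-up is clocked from birth, and the adjustment rule does not name entry stage

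*Protocol article*

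**What the plan says.** Entry: the Participants section admits women who are "pregnant or have a baby no older than 2 months of age" and "already enrolled in the Family Spirit program in their community". The Inclusion criteria repeat the same upper limit and set no minimum gestational age. The Standard Family Spirit section adds that "the duration of enrollment for this pilot study is from pregnancy to 12 months postpartum".

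Baseline: the Abstract bounds it only from above: "Data is collected at baseline (< 2 months postpartum), and 2, 6, and 12 months postpartum". In practice it appears to follow consent, since "The first participant gave consent on June 25, 2019, and the first baseline assessment was completed on June 26, 2019" (Exclusion criteria section).

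Follow-up: the Data collection time points section fixes the later visits relative to birth: "All participants will be assessed at four timepoints: baseline, 2 months, 6 months, and 12 months postpartum".

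Instruments: Table 2 places seven secondary measures at both baseline and 2 months: ASSIST, EPDS, Parent Knowledge Assessment, EuroQol, Perceived Stress Scale 4, the Integrated Screening Tool and Top Problems. The Working Alliance Inventory (WAI) has no baseline administration and is first taken at 2 months. Acceptability is "administered at study midpoint and endpoint", and satisfaction follows the same timing.

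Analysis: the Primary aim analysis section models the interaction of arm with change in each score, with random effects for person and site. The adjusted analyses cover baseline demographics that differ between arms at p < 0.1. Secondary outcomes are declared exploratory.

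**The concern.** Entry and the start of the study strategy run on one clock (consent), and follow-up runs on another (birth). A mother who consents with a seven- or eight-week-old infant completes baseline and the 2-month battery within days. A mother who consents early in pregnancy has most of a year between the same two visit labels.

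Two consequences follow. First, baseline depression, stress, substance use and quality of life are prenatal values for some mothers and postpartum values for others, and the interval over which they can change varies widely. Second, the first WAI score means different things. For a late entrant in the precision arm it is close to a pre-exposure measurement of a relationship that already existed. For a mother enrolled in pregnancy it follows months of the strategy, so an effect already present sits inside the first value from which change can be measured.

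Individual randomization would balance entry timing on average. Here four sites were allocated by coin flip after matching on client volume and on urban or rural setting, so nothing in the design balances it. The pilot is meant to supply variability and effect estimates for a larger trial, and a mix of two kinds of baseline would carry into those estimates.

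**Working it through.** There is no figure in the plan to reproduce; the check is on timing.

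**Inputs.** Follow-up at 2, 6 and 12 months after birth (Data collection time points). Entry from pregnancy, with no lower limit, to infant age 2 months (Participants; Inclusion criteria). Assumptions, not in the article: a 40-week term, 30.44 days per month, baseline at consent, and gestational age at entry, shown as a range.

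**Formula.** Gap in months = follow-up age − infant age at baseline. For entry in pregnancy, infant age at baseline = −(40 − gestational weeks) × 7 / 30.44.

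Example, entry at 12 weeks: (40 − 12) × 7 / 30.44 = 6.4 months before birth, so the gap to the 2-month visit is 6.4 + 2 = 8.4 months.

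| Entry | To 2-month visit | To 6 months | To 12 months |
|---|---|---|---|
| 8 weeks' gestation | 9.4 | 13.4 | 19.4 |
| 12 weeks' gestation | 8.4 | 12.4 | 18.4 |
| 20 weeks' gestation | 6.6 | 10.6 | 16.6 |
| 28 weeks' gestation | 4.8 | 8.8 | 14.8 |
| 36 weeks' gestation | 2.9 | 6.9 | 12.9 |
| At birth | 2.0 | 6.0 | 12.0 |
| Infant 1 month | 1.0 | 5.0 | 11.0 |
| Infant 1.9 months | 0.1 | 4.1 | 10.1 |
| Infant exactly 2 months | 0 | 4.0 | 10.0 |

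In days, 2 months is 60.9. Entry at 7 weeks leaves 60.9 − 49 = 11.9 days, and entry at 8 weeks leaves 60.9 − 56 = 4.9 days. The short end therefore follows from the article's own limits. Only the long end needs an assumed gestational age.

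**Which outcomes are touched.** Seven secondary instruments appear at both baseline and 2 months in Table 2. The Secondary outcomes text would make it eight, because it places Parental Locus of Control at every time point while Table 2 lists it at 6 and 12 months only. Among the primary assessment scores, only the WAI is taken at 2 months. At 6 and 12 months even the latest entrant has about 4 and 10 months of exposure, so the vulnerable score is one of three.

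**How it could reach the arm comparison.** Let S be the difference in mean change between mothers enrolled in pregnancy and mothers enrolled after birth, and let p1 and p0 be the proportions enrolled in pregnancy in the two arms. With no true arm effect, the unadjusted arm difference in change is (p1 − p0) × S. The article gives neither quantity, so no size can be attached. The product vanishes only if the arms have the same entry mix or entry stage does not matter.

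**Whether the stated rule catches it.** The p < 0.1 screen is described for baseline demographics. Entry stage is not named as one of them. Even if it were screened, a difference large enough to matter could miss that threshold with 60 mothers.

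**The case against.** Several points on the other side stand. Clocking follow-up from birth is sensible, because the child feeding and ASQ measures depend on infant age, and the arms can still be compared at the same infant age. The EPDS is described as designed for pregnant women as well as new mothers. Secondary outcomes are exploratory. Detailed visit windows and the coding of time are commonly left to a full protocol or analysis plan, so their absence is not a fault. The authors already concede that four sites are unlikely to give fully comparable groups.

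It can also be argued that the Abstract's wording places baseline after birth for everyone. The gap would then run only from 0 to 2 months and the prenatal/postpartum mix would disappear. That sits poorly with participation beginning in pregnancy and with tailoring on needs found at baseline. The overlap at the short end, and the unequal exposure before the first WAI, would remain under that reading.

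Four stronger inferences are tempting and are not supported:

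- That the plan analyses change from baseline for its primary outcomes. The article does not say so, and acceptability, satisfaction and the WAI have no baseline value.
- That all mothers are treated as having the same interval. The time variable is not defined, so this cannot be read from the text.
- That an early effect would be diluted by 20% to 40%. This takes a fraction f of late entrants between 0.2 and 0.4, with no effect in them and the full effect in all others. The article gives no basis for f and does not single out a 2-month contrast.
- That late entrants should skip the 2-month assessment. The WAI, child feeding and ASQ measures all start there and would be lost.

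**Conclusion.** The point holds in a limited form. The stated entry and baseline window abuts the 2-month visit and, where the limit is worded as no older than 2 months, touches it. The gap is 0 at the short end on the article's own terms and about 8 to 9 months at the long end for entry at 8 to 12 weeks' gestation, which is an assumption. The effect is confined to the seven exploratory instruments measured at both points and to the first of three WAI scores. The bias risk is conditional: it needs the sites to differ in entry timing, which the article neither shows nor rules out. Because allocation is by site and the stated covariate screen does not name entry stage, nothing in the described analysis guards against it. This is a worthwhile, nearly free improvement, not a flaw that undermines the pilot.

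**What to change.** 1. Keep the 2-month assessment for every participant.
2. Name entry stage (pregnant or postpartum at consent) in advance as a fixed covariate in the adjusted outcome models, whatever the p < 0.1 screen shows.
3. Record weeks from consent to each assessment, and report entry stage by site and by arm.
4. Add one sensitivity analysis. For mothers whose baseline falls within a pre-set interval of the 2-month visit, either exclude the 2-month values of the repeated instruments and the 2-month WAI, or treat them as start-of-study values. The interval is for the sponsor to set before seeing outcome data. Four weeks, as an illustration, would capture baselines taken at an infant age of about 33 days or later (60.9 − 28).

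The cost is small. Consent and birth dates are already needed for enrolment and for scheduling birth-anchored visits, and no assessment is added or removed. The adjusted models carry one more term with N = 60, and the sensitivity analysis uses slightly less 2-month information. The covariate handles differences in entry mix only; other differences among four sites remain.

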**Discussion:**

This trial will provide new information about the acceptability and feasibility of precision home visiting and pilot data on program satisfaction, client-home visitor relationship, goal alliance, retention, and targeted maternal-child intervention outcomes. Findings will inform the design of a fully powered randomized implementation trial of precision vs. standard home visiting.

**Trial registration:**

ClinicalTrials.gov #NCT03975530; Registered on June 5, 2019

**Supplementary Information:**

The online version contains supplementary material available at 10.1186/s40814-020-00753-4.

## Key messages on feasibility

Prior to this pilot study, it is unclear whether comparing a modularized version of a home visiting program to standard practice home visiting would be feasible, and, if so, whether there would be detectable differences between the approaches.Results will inform whether and how to design a fully powered randomized controlled trial to test implementation effectiveness of a modularized version of home visiting to improve primary outcomes*.*The results of the study will inform 1) how to approach randomization, 2) data collection platforms to use, 3) sample size calculations, and 4) adaptations to the design and measures for a fully powered randomized controlled trial.

## Background

Decades of research validate early childhood home visiting as an effective strategy to support families. Home visiting programs target a range of maternal and child outcomes, including promoting healthy growth and development, and reducing maternal and child behavioral and mental health disparities. In 2010, the United States Congress authorized $1.5 billion to fund the Maternal, Infant, and Early Childhood Home Visiting (MIECHV) Program across the United States (US). MIECHV was reauthorized and funded at $400 million per year for 5 years in early 2018. The Home Visiting Evidence of Effectiveness (HomVEE) review identified 21 home visiting models that meet the US Health and Human Services criteria for an evidence-based early childhood home visiting service delivery model. Of these, 19 are eligible to be used with MIECHV funds [1, 2].

Evidence-based home visiting programs being disseminated across the US struggle with retention of families. A recent report indicated only half of participating families across four home visiting models remained in the program at one year postpartum, despite these models expecting that families remain enrolled until at least 2 years postpartum [3]. Many home visiting models were designed to serve families over several years with regularly scheduled visits. While some shorter home visiting models have seen positive outcomes, little is known regarding optimal duration and dosage [4]. Moreover, the types of families being served and the diversity of issues and challenges they present suggest the need to tailor and adapt programs to better fit a wide range of needs [5]. To date, this tailoring has almost always relied solely on the judgement of an individual home visitor or, in some cases, is guided by the implementing organization without guidance from the model developer.

Recent qualitative research on high- and low-retention sites using one evidenced-based home visiting model showed that nurses in high-retention sites were more collaborative with families. They were more likely to adapt their program delivery to align with families’ needs, compared to nurses in low-retention sites [6]. Based on these findings, Ingoldsby and colleagues (2013) developed an implementation strategy grounded in the principals of motivational interviewing to provide nurses with more explicit control over the visit schedule and content to families. When they compared retention rates for nurses trained in motivational interviewing to rates for nurses trained in the standard approach, preliminary findings showed retention rates were significantly better when nurses had more flexibility in service delivery [7]. It is important to note that authors recognized several other factors that may be influencing these positive findings. Nonetheless, improving implementation of programs at scale including achieving high participant retention, enhancing program content to address families’ unique and complex needs, and increasing model fidelity is of key interest to researchers, implementing agencies, and other stakeholders [8].

From 2016 through 2018, the Johns Hopkins Center for American Indian Health (CAIH) conducted formative work to develop an implementation strategy for *Family Spirit®* based on concepts of design modularity [9]. Design modularity aims to systematically tailor content to meet families’ needs. Family Spirit is a federally endorsed, evidence-based model designed for, by, and with Native American communities [10–12]. The rationale for the development of a precision implementation strategy for Family Spirit, called Precision Family Spirit, was based on two factors. First, home visitors are faced with the complex task of applying knowledge gained from previous research studies to a diverse range of clients who may be substantially different from the populations from which this research was generated. This yields potential problems with fidelity. Second, based on studies indicating tailoring may help with retention [6, 7], we sought to use modularization as an implementation strategy to tailor Family Spirit while maintaining fidelity to the model [13].

The current study is a pilot Hybrid Type 3 [14] implementation trial of Precision Family Spirit. This hybrid design tests an implementation strategy while also gathering data on relevant outcomes. This pilot study will examine the acceptability, feasibility, and preliminary effects of a “precision approach” to home visiting. Our specific aims are to 1) explore the acceptability and feasibility of a precision approach to home visiting from the perspective of enrolled mothers and 2) examine the difference between *Precision Family Spirit* and *Standard Family Spirit* on program satisfaction, client-home visitor relationship, goal alliance, and retention. As part of the hybrid design, we will also monitor client level intervention effects on maternal self-efficacy, stress, and child social, emotional, and behavioral development.

